### Randomization, Blinding, and allocation

Participants are randomly assigned to the vitamin C or normal saline (NS) groups in a 1:1 ratio. The randomization sequence is generated with SAS v. 9.2 (SAS Institute Inc., United States) using stratified block randomization with a block length of 10 and stratified by site. A randomized envelope is made by a statistician in our clinical research center. The sequence number is marked outside the envelope and the medication puzzled for vitamin C or NS is sealed inside. The randomization information is blinded to all the participants in the trials except the unblinding drug preparing nurse (UDPN).

After consent is obtained and the inclusion/exclusion criteria are verified, the principal investigator (PI) in each participating site (PS) hands the unique randomized envelope of the participant to UDPN. The UDPN unseals the envelope and disposes the vitamin C or NS into an opaque 50 ml syringe according to grouping information inside the envelope. UDPN gives the opaque syringe to the therapy nurse and is independent of the following medical process. The outcome assessor and statistician are blinded to randomization and are not involved in treatment procedures.

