### Sample size

The sample size calculation is based on the primary outcome of 28 days of mortality in patients with sepsis. It was estimated that the sepsis mortality rate within 28 days would be 40%. We used the superiority test for two proportions based on the one-sided 2.5% of type I error probability and 80% of power. A total of 620 participants are required to detect a decrease of 10% mortality rate and 10% dropout rate. The sample size was calculated by PASS 15 software (NCSS, Kaysville, UT, United States).

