### Statistical analysis

Categorical data will be described with frequency or ratio. Continuous variables will be described using mean and SD for normally distributed variables or median and interquartile range (IQR) for non-normally distributed variables. Categorical variables will be compared using the chi-square test or the Fisher exact test. Continuous variables will be compared using the t-test for normally distributed variables or the Wilcoxon rank-sum test for non-normally distributed variables. The efficacy analysis will be based on the intention-to-treat principle and compared with the per-protocol principle subset.

The primary outcome of 28 days mortality will be compared between groups using the chi-square test or the Fisher exact test. Superiority could be calculated if the upper bound of 28 days of mortality was lower than the 2.5% superiority margin. Logistic analysis with a 95% CI is used to calculate the odds ratio of each risk factor.

The secondary outcomes of the SOFA score change and inflammatory indicators change on days 1, 3, 7, 14, and day 28 between two groups will be analyzed using a generalized linear model. The incidence of organ failure and adverse events occurrence will be compared using the chi-square tests or the Wilcoxon rank-sum test. The duration of organ support and vitamin C concentration on days 0, 3, 4, and day 7 will be compared using the *t*-test or the Wilcoxon rank-sum test. All these analyses are performed two-sided at the 5% significance level. SAS v. 9.2 (SAS Institute Inc., United States) is used for the analysis.

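### The superiority rule for 28-day mortality is unusable as written: its bound has no contrast, confidence level or direction, and its 2.5% margin has no counterpart in the sample size

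*Protocol article*

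**What the plan says.** The Statistical analysis section of the Protocol article gives two consecutive statements on the primary outcome. The first is a test: "The primary outcome of 28 days mortality will be compared between groups using the chi-square test or the Fisher exact test". The second is a decision rule: "Superiority could be calculated if the upper bound of 28 days of mortality was lower than the 2.5% superiority margin". The section later adds: "All these analyses are performed two-sided at the 5% significance level".

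The Sample size section describes the design: "We used the superiority test for two proportions based on the one-sided 2.5% of type I error probability and 80% of power". It assumes 28-day mortality of 40% and continues: "A total of 620 participants are required to detect a decrease of 10% mortality rate and 10% dropout rate". It mentions no margin. The figure 2.5% occurs there once, as the one-sided type I error. Allocation is 1:1 (Randomization, Blinding, and allocation).

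**The concern.** The rule lacks three things that a confidence-limit criterion needs: the quantity bounded, the confidence level, and the sign of the threshold. As worded, it bounds mortality itself rather than a difference between groups.

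The margin also has no source. A chi-square or Fisher test has a null of no difference, and the sample size is described as an ordinary superiority test of two proportions. A margin of 2.5% in either direction is a different hypothesis from both. The article does not say whether the test decides, the margin rule decides, or both must be met.

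This threshold determines whether the trial is called positive on mortality. If it stays open, the choice between rules could be made after the results are known, and for some results that choice would change the conclusion.

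**Working it through.** **Inputs.** Control mortality 40%, a decrease of 10% read as absolute (to 30%), 80% power, one-sided 2.5%, 10% dropout and 620 in total (Sample size); 1:1 allocation; two-sided 5% (Statistical analysis). This gives 310 per arm randomised and 279 per arm after 10% dropout (558 = 0.9 × 620). Let d = mortality on vitamin C minus mortality on saline, with a two-sided 95% CI and normal approximation.

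**The plan's own figure.** With zero margin and one-sided 2.5%, the pooled formula gives
n = [1.960·√(2 × 0.35 × 0.65) + 0.842·√(0.24 + 0.21)]² / 0.10² = 356 per arm, so 712 evaluable and 712/0.9 = 792 (rounded up). The stated 620 is not reproduced. It is met exactly by one-sided 5% with unpooled variance: 279 per arm, 558/0.9 = 620. That is a separate matter, but it affects the power comparison below.

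Does a margin explain 620? With n = 7.849 × 0.45 / (m + 0.10)² for the rule *upper limit of d below m*:
- m = +0.025: 7.849 × 0.45 / 0.125² → 227 per arm, 454 evaluable, 505 with dropout.
- m = -0.025: 7.849 × 0.45 / 0.075² → 628 per arm, 1256 evaluable, 1396 with dropout.

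Neither does. At one-sided 5% the totals with dropout are 398 and 1100.

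**Reading A: one arm's mortality, upper limit below 2.5%.** The exact (Clopper-Pearson) upper limit falls below 2.5% only with at most 2 deaths in 310, or 1 in 279. At 30% mortality the probability is about 10⁻⁴⁴ and 10⁻⁴¹ respectively.

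**Reading B: d, upper limit below +2.5%, used alone.** With 40% in both arms, SE = √(2 × 0.4 × 0.6 / n), which is 0.0415 (n = 279) or 0.0394 (n = 310).
P(declare) = Φ(0.025/SE - 1.96) = Φ(-1.357) = 8.7% or Φ(-1.325) = 9.3%, instead of 2.5%.

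**Reading C: d, upper limit below -2.5%.**
- No effect: Φ(-0.025/SE - 1.96) = about 0.5% at either size.
- 40% versus 30%: SE = √(0.45/n), which is 0.0402 or 0.0381. Power = Φ(0.075/SE - 1.96) = 46% (n = 279) or 50% (n = 310).

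**Comparator: zero margin, two-sided 5%.** Power of the pooled test = Φ([0.10 - 1.96·√(0.455/n)] / √(0.45/n)) = 70% (n = 279) or 74% (n = 310). The loss due to a -2.5% margin is therefore about 24 points.

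**Where the rules part.** Observed reduction needed, using the 40% SE (threshold = 1.96 × SE - m):

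| Rule | n = 279 | n = 310 |
|---|---|---|
| upper limit below +2.5% | 5.6 points | 5.2 points |
| upper limit below 0 | 8.1 points | 7.7 points |
| upper limit below -2.5% | 10.6 points | 10.2 points |

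For n = 279, a reduction between 5.6 and 8.1 points passes Reading B and fails the test against zero. A reduction between 8.1 and 10.6 points passes the test against zero and fails Reading C.

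**The case against.** The strongest reply is that this is a slip of wording. The 2.5% is probably the one-sided alpha from the Sample size section, mislabelled as a margin, and the intended rule is the ordinary one. That is plausible. But the sentence says "lower than the 2.5% superiority margin", and recovering the ordinary rule means replacing those words, so the origin explains the error without removing it. The article states this rule outright, so it is not detail left to an analysis plan.

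Four stronger inferences are tempting, and the document does not support them.

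- *Every reading leads to a wrong decision.* Reading C is a legitimate, stricter superiority test with a false-positive rate of about 0.5%. Its faults are low power and possible disagreement with the chi-square test.
- *The type I error is inflated.* That follows only if the margin is +2.5% and that rule alone decides. If the chi-square test must also be met, the +2.5% condition adds nothing: a significant result favouring vitamin C already puts the upper limit at about 0 or lower. Reading B also sits badly with the superiority label used throughout the article.
- *The rules can give opposite conclusions.* Under either difference reading they are nested: one declares superiority where the other does not. They cannot show benefit on one and harm on the other. Significant harm would put the upper limit above about 2 × 7.7 = 15.4 points, far beyond +2.5.
- *Power falls from 80% to 46%.* The zero-margin test has only 70% to 74% at this size, so the margin accounts for about 24 points. The rest comes from 620 not following from one-sided 2.5%.

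**Conclusion.** The point holds in this form: the stated superiority rule is wrong as written and cannot be applied without rewriting. The bound is undefined, the margin has no basis in the sample size, and its relation to the chi-square or Fisher test is not given. No other section of the article repairs it.

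The consequences depend on the reading: practically impossible to meet (A); 8.7% to 9.3% false declarations instead of 2.5%, if used alone (B); 46% to 50% power against 70% to 74% (C). None of these is established as what the trial will do. The correction is needed because this is the primary decision rule, not because inflation or loss of power has been shown.

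The figures assume an absolute decrease of 10 points, a two-sided 95% CI, the normal approximation, and 279 to 310 evaluable per arm. Fisher's test would differ slightly from the chi-square test in borderline cases.

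**What to change.** Before any unblinded look at outcome data, replace the sentence with: *Superiority is concluded if the upper limit of the two-sided 95% CI for the 28-day mortality risk difference (vitamin C minus NS) is below 0.* Delete the 2.5% margin. This agrees with the two-sided 5% level in Statistical analysis, with the one-sided 2.5% in Sample size and, borderline cases apart, with the chi-square test.

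If a margin was truly intended, state its sign and justification, say how it combines with the chi-square or Fisher test, and restate the power it leaves at 620.

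The first option costs one sentence in an amendment or the analysis plan. It needs no new data and no change to trial conduct, and the Monitoring section places the analysis at study completion. It does not resolve the separate mismatch between 620 and one-sided 2.5%.

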#### Secondary outcomes

The secondary outcomes are as follows:

1.The incidence of organ failure within 28 days: organ failure is defined as at least three points on the SOFA score assigned in a particular organ system (cardiovascular, hepatic, respiratory, renal, and coagulation system) (18).2.Change in the SOFA score on days 1, 3, 7,14, and 28.3.The duration of organ support within 28 days: Organ support is defined as mechanical ventilation, renal replacement therapy, and vasoactive drug application.4.Plasma concentration of vitamin C on days 0, 3, 4, and 7 and its relationship with outcomes and adverse events5.The change of inflammatory indicators (C-reactive protein and procalcitonin) on days 1, 3, 7, 14, and 28.

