### Data collection

All data are collected using a web-based database in each participating center (Table 1). When participants are withdrawn from the study, they are not replaced. Patients that are lost during the study period will be incorporated into the analysis until their final lost date. Missing data are replaced by chained equations using multiple imputations if these missing data are judged to be random.

**TABLE 1 T1:** Collected data and outcomes.

Procedures	Day 0	Day 1	Day 3	Day 4	Day 7	Day 14	Day 28
Eligibility criteria	X						
Informed consent	X						
Demographic and medical data	X						
Vital signs							
Fluid balance							
Routine laboratory test*							
Inflammatory indicators #	X	X	X	X	X	X	X
Plasma vitamin C concentration	X		X	X	X		
SOFA score	X	X	X	X	X	X	X
APACHEII score	X						
Organs support							
Vasoactive drugs							
Adverse events							
Death							X
Hospital stay							X

*Routine laboratory tests include the following: white blood cell (WBC) count, hemoglobin, thrombocytes, blood gas analysis, electrolytes, urea, creatinine, aspartate transaminase, alanine transaminase, lactate dehydrogenase, alkaline phosphatase, NT-proBNP, TnI, and coagulation test. #Inflammatory indicators include the following: C-reactive protein (CRP) and procalcitonin (PCT). SOFA, Sequential Organ Failure Assessment; APACHEII, Acute Physiology And Chronic Health Evaluation II.

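### SOFA, CRP and PCT changes at five visits are assigned to a generalized linear model with no stated handling of repeated measurements and no day-0 covariate

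*Protocol article*

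**What the plan says.** Secondary outcomes lists the change in SOFA score on days 1, 3, 7, 14 and 28, and "The change of inflammatory indicators (C-reactive protein and procalcitonin) on days 1, 3, 7, 14, and 28". Each patient can therefore supply up to five change scores on each of three variables.

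Statistical analysis gives the method: these changes "on days 1, 3, 7, 14, and day 28 between two groups will be analyzed using a generalized linear model". Of this family of analyses it adds that "All these analyses are performed two-sided at the 5% significance level". It names no random effect, estimating equation, covariance structure or covariate, and does not say whether the days are modelled together or separately.

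Table 1 shows that the baseline values are available. SOFA is marked at all seven time points from day 0 to day 28 ("SOFA score X X X X X X X"), and so are the inflammatory indicators, which its footnote defines as CRP and PCT.

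**The concern.** In its standard form a generalized linear model treats every row as an independent observation. Five change scores from one patient are not independent: they come from the same person and all subtract the same day-0 value. If all rows enter one such model, the standard error of the average arm effect is too small, so false positives become more frequent and confidence intervals too narrow.

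Fitting the model separately on each day avoids that problem but leaves 3 variables × 5 days = 15 comparisons at 5%, with no day identified as the main one.

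Under either reading, the day-0 value is used only by subtraction. As a covariate it would give a more precise estimate of the same arm difference.

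**Working it through.** **Plan's own figure.** The article gives no figure for this analysis. Its sample size of 620 concerns 28-day mortality and is used here only to set 310 patients per arm in the simulation.

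**Inputs.** From the documents: five post-baseline visits, three variables, two-sided 5%, 1:1 allocation. Assumed, because the documents give no value: an exchangeable within-patient correlation ρ between the five change scores, taken as 0.3, 0.5 and 0.7. The middle value has some basis. If the raw scores have equal variance and a common correlation r, two changes sharing one baseline have covariance 1 − r and variance 2(1 − r), so they correlate at 0.5 whatever r is.

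**Reading A: all visits pooled as independent rows.** For the average arm effect over m = 5 visits, the design effect is DE = 1 + (m − 1)ρ. The true standard error is √DE times the reported one, and the type I error is 2[1 − Φ(1.96/√DE)].

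| ρ | DE | √DE | Type I error | 95% CI coverage |
|---|---|---|---|---|
| 0.3 | 1 + 4(0.3) = 2.2 | 1.48 | 19% | 81% |
| 0.5 | 1 + 4(0.5) = 3.0 | 1.73 | 26% | 74% |
| 0.7 | 1 + 4(0.7) = 3.8 | 1.95 | 31% | 69% |

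A simulation (310 per arm, no treatment effect, no deaths or missing values, 4,000 runs at each of three raw-score correlations) agrees. On change scores the pooled model rejected in 25% to 26% of runs. The same contrast with patient-level standard errors rejected in 4.5% to 5.2%.

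The error depends on the contrast. In the pooled model an arm-by-time contrast has type I error 2[1 − Φ(1.96/√(1 − ρ))], which is 0.6% at ρ = 0.5. That test is too conservative.

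**Reading B: one model per day.** Each test is valid: the simulated per-visit comparison rejected in 4.8% to 5.5% of runs. What remains is the number of tests. The chance of at least one false positive would be 1 − 0.95^5 = 23% within one variable and 1 − 0.95^15 = 54% across all three if the tests were independent. They are correlated, so these are upper figures.

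**Baseline, under either reading.** Take the raw score with SD 1 and correlation r between day 0 and follow-up. The variance of a change score is 2(1 − r). The residual variance after adjustment for the day-0 value is 1 − r².

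- r = 0.5: 2(0.5) = 1.00 versus 1 − 0.25 = 0.75.
- r = 0.7: 2(0.3) = 0.60 versus 1 − 0.49 = 0.51.

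Adjustment therefore cuts the variance at a visit by 25% and 15% respectively (0.09/0.60 = 15%).

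**The case against.** The strongest reply is that the article is a condensed account. It does not say that visits are pooled as independent rows, nor that correlation is ignored. Estimating equations extend the generalized linear model and are a routine way to fit it to repeated data, so the wording is compatible with a correct analysis that the full protocol or analysis plan may set out. The phrase about comparing two groups on listed days also fits one model per day. This reply stands. The article's usual rule for continuous variables is a t-test or rank-sum test, which it also applies to vitamin C concentration on several days. The switch to a model for SOFA, CRP and PCT hints at a joint analysis of the five days but does not prove it.

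Four stronger inferences are tempting, and the documents do not support them:

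- A reader might infer that the p-values and intervals are wrong. That is so only under Reading A.
- A reader might infer that baseline is ignored. It enters by subtraction, and in a randomized comparison the missing covariate costs precision, not validity.
- A reader might take 54% as the actual false-positive risk. It needs 15 independent tests.
- A reader might call the absence of day 4 from the analysis a contradiction, because Table 1 collects these variables then. Secondary outcomes and Statistical analysis list the same five days, and collecting a further day conflicts with neither.

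Log-transforming CRP and PCT, or naming a single main contrast, would likewise be a choice and not the correction of an error.

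**Conclusion.** The point holds as a conditional weakness with a better alternative that needs no new data. As written, the method leaves open an analysis whose average-effect test would have about 19% to 31% type I error at assumed correlations of 0.3 to 0.7. The other natural reading gives valid individual tests but 15 of them, with no main time point. Under both, adding the day-0 value already collected would improve precision without changing the quantity estimated.

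The sizes rest on assumed correlations, an exchangeable structure and complete data at five visits. The article expects substantial 28-day mortality ("It was estimated that the sepsis mortality rate within 28 days would be 40%"), so many patients will contribute fewer visits, and the inflation under Reading A would then be smaller. With three visits and ρ = 0.5, for example, DE = 1 + 2(0.5) = 2 and the error is 2[1 − Φ(1.96/1.41)], about 17%. Only secondary outcomes are concerned; the primary mortality comparison is unaffected.

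**What to change.** For each of SOFA, CRP and PCT, fit one repeated-measures model: either a mixed model with unstructured covariance or generalized estimating equations with robust standard errors. Include arm, visit, arm-by-visit, the day-0 value and site, which is the randomization stratification factor. Report the arm difference at each visit with its confidence interval. The day-4 values already collected under Table 1 can be included if wished.

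The cost is a few sentences in the analysis plan and standard SAS procedures. No new data, visits or patients are needed. If the full plan already specifies such a model, saying so in place of the bare term would be enough.

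### Organ-support duration is compared as raw days with no role for death, in a trial planned for 40% versus 30% mortality, so the result mixes time to death with organ recovery

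*Protocol article*

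**What the plan says.** The Secondary outcomes section of the protocol article defines the endpoint as "The duration of organ support within 28 days: Organ support is defined as mechanical ventilation, renal replacement therapy, and vasoactive drug application". It is a plain count of days with no term for patients who die. The Statistical analysis section fixes the comparison: "The duration of organ support and vitamin C concentration on days 0, 3, 4, and day 7 will be compared". The method named is a t-test or a Wilcoxon rank-sum test, two-sided at 5%. The same section bases the efficacy analysis on intention to treat.

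The Sample size section assumes 40% mortality at 28 days and states "A total of 620 participants are required to detect a decrease of 10% mortality rate and 10% dropout rate". Allocation is 1:1.

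The Data collection section has two rules for incomplete data. Lost patients contribute until the date they are lost. For the rest, "Missing data are replaced by chained equations using multiple imputations if these missing data are judged to be random". Neither rule mentions death.

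**The concern.** Support days stop accruing when a patient dies. Someone who dies on day 3 while ventilated contributes 3 days; someone who is ventilated for 10 days and goes home contributes 10. Fewer days reads as the better outcome, so the ranking puts the death ahead of the recovery.

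This would matter little if deaths were rare or equal between arms. Here they are expected in 30% to 40% of patients, and the planned benefit is itself a difference in deaths. If vitamin C works as hoped, the arms will differ in how many patients have their support time cut short by death. The duration comparison would then shift even if the drug did nothing to the speed of organ recovery. Depending on when patients die, that shift could make a life-saving drug look as if it prolongs support, or a harmful one look as if it shortens it.

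**Working it through.** **Inputs from the article.** Control mortality is 40%. I read the 10% decrease as absolute, giving 30%; a relative decrease (to 36%) would need about 4,622 patients before dropout, far from 620. Half of 620 is 310 per arm. Expected deaths are 0.40 × 310 = 124 and 0.30 × 310 = 93. The article gives no figure for support duration, so there is none to reproduce.

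**Assumed inputs.** Mean support days in survivors (S) and non-survivors (D) are not in the article. I take exponential durations capped at 28 days, S = 10 before capping and D from 3 to 14. The drug has no effect on support within either group, and there is no dropout.

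**Expected shift.** With mortality p, mean duration over all patients is p·D + (1 − p)·S. The drug-minus-control difference is (0.40 − 0.30)·(S − D) = 0.10·(S − D). It is positive (drug looks worse) only if non-survivors have fewer support days than survivors.

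Uncapped, with D = 5 and S = 10: control 0.4 × 5 + 0.6 × 10 = 8.0; drug 0.3 × 5 + 0.7 × 10 = 8.5; difference +0.5 day.

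Capping at 28 turns a mean m into m·(1 − e^(−28/m)), so S = 10 becomes 9.39. Monte Carlo runs of 310 per arm with the Wilcoxon test give the last column.

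| D before cap | D after cap | Control mean | Drug mean | Difference | Trials with a significant result |
|---|---|---|---|---|---|
| 3 | 3.00 | 6.83 | 7.47 | +0.64 | longer on drug in about 20% |
| 5 | 4.98 | 7.63 | 8.07 | +0.44 | longer in about 10%, shorter in 0.3% |
| 7 | 6.87 | 8.38 | 8.63 | +0.25 | longer in about 5%, shorter in 1.3% |
| 10 | 9.39 | 9.39 | 9.39 | 0 | longer in 2.5%, shorter in 2.6% |
| 14 | 12.11 | 10.48 | 10.21 | −0.27 | shorter in about 5% |

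A two-sided 5% test with no bias gives 2.5% in each direction, so the 10-day row is chance level, and the 7-day and 14-day rows are about twice chance in one direction.

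**Harm.** With D = 5 and the mortality rates reversed (30% on control, 40% on drug), the harmful drug shows significantly shorter support in about 10% of trials.

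**A second model.** Here the sickest patients die, support need rises with severity, and mean time to death is varied. For a cut from 40% to 30%, the difference over all patients is +0.54, +0.34, +0.14 and −0.10 days at 3, 5, 7 and 10 days to death. The t-test finds support significantly longer in 39%, 16% and 6% of trials for the first three. With mortality raised to 50%, the differences at 3, 5 and 7 days are −0.45, −0.26 and −0.07. The pattern is the same, including the change of sign.

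**Alternative endpoint, first model.** Score death by day 28 as 0 support-free days and a survivor as 28 minus support days. Survivors average 28 − 9.39 = 18.61. Control is 0.6 × 18.61 = 11.2 and drug 0.7 × 18.61 = 13.0. The difference has the right direction whatever D is, because D no longer enters, and it is significant in about 54% of trials.

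**The case against.** Four objections deserve an answer.

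**Direction.** A reader might infer that the endpoint necessarily moves against an effective drug. The article does not support that. The shift has that sign only if non-survivors accrue fewer support days than survivors; it is nil when they are equal and reverses when non-survivors are supported longer. This objection stands in full. It does not rescue the endpoint, whose behaviour then depends on when patients die.

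**Condensed article.** Handling of deaths is often left to an analysis plan. For organ-support duration this does not answer the point, because the article itself fixes both the raw-days outcome and its tests. For change in SOFA, C-reactive protein and procalcitonin it largely does. A reader might infer that values after death would be multiply imputed, but the stated rule covers only data judged to be random, and nothing says post-death values would be so judged. What remains is a request for one clarifying sentence.

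**Organ failure.** A reader might extend the criticism to this outcome, where "organ failure is defined as at least three points on the SOFA score assigned in a particular organ system". The article gives no basis for a size, and many septic deaths would pass through that threshold first. Failure already present on day 0 is a separate matter of definition, expected to balance under randomisation. I do not press either.

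**The replacement counts mortality.** In the first model survivors' support is unaffected by the drug, so the 54% detection is the mortality benefit counted again. It does not show that the composite measures organ recovery better. This stands and must be acknowledged in reporting.

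**Conclusion.** The point holds for organ-support duration. The article fixes a raw count of days, tested by t-test or Wilcoxon, that rewards early death in a trial expecting about 124 and 93 deaths per 310. The comparison cannot be read as organ recovery alone.

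The size is moderate and conditional. Across the assumed range of 3 to 14 support days in non-survivors against 10 in survivors, the mean shift runs from +0.64 through zero to −0.27 day. The chance of a significant result unrelated to recovery runs from about 20% for longer support to about 5% for shorter. The mortality inputs come from the article; the support durations, their exponential shape and the absence of a drug effect on survivors are assumptions.

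This is a secondary outcome, and mortality would be reported beside it. The change should be made, but the trial's main conclusion does not depend on it.

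**What to change.** Replace the outcome with days alive and free of each support (mechanical ventilation, renal replacement therapy, vasoactive drugs) to day 28, scoring death by day 28 as 0. Compare arms by Wilcoxon rank-sum test or a proportional-odds model. Report 28-day mortality and support duration in survivors beside it as descriptive components.

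As a secondary clarification, state that SOFA, C-reactive protein and procalcitonin values after death are not to be filled in under the multiple-imputation rule in Data collection.

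The cost is wording and derivation. Death and organ support are already in the article's table of collected data, and Monitoring places the analysis at study completion, so the change can be made before unblinding. The downside is that the composite partly reflects mortality: a difference in support-free days is not by itself evidence of faster organ recovery, and the report should say so.
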